## Abstract

**Introduction::**

The morbidity and mortality of acute myocardial infarction patients still remains high after percutaneous coronary intervention (PCI). Myocardial ischemia-reperfusion (MIR) injury is one of the important reasons. Although the phenomenon of MIR injury can paradoxically reduce the beneficial effects of myocardial reperfusion, there currently remains no effective therapeutic agent for preventing MIR. Previous studies have shown that Yiqi Liangxue Shengji prescription (YLS) is effective in improving clinical symptoms and ameliorating the major adverse cardiovascular events of coronary heart disease patients undergoing PCI. This study aims to evaluate the effectiveness and safety of YLS in patients with acute myocardial infarction (AMI) after PCI.

**Methods::**

This study is a randomized, double-blinded, placebo-controlled, single-central clinical trial. A total of 140 participants are randomly allocated to 2 groups: the intervention group and the placebo group. Based on routine medications, the intervention group will be treated with YLS and the placebo group will be treated with YLS placebo. All participants will receive a 8-week treatment and then be followed up for another 12 months. The primary outcome measures are N terminal pro B type natriuretic peptide (NT-proBNP) and left ventricular ejection fraction. Secondary outcomes are plasma levels of microRNA-145, plasma cardiac enzyme, and Troponin I levels in blood samples, changes in ST-segment in ECG, Seattle Angina Questionnaire, the efficacy of angina symptoms, and occurrence of major adverse cardiac events. All the data will be recorded in case report forms and analyzed by SPSS V.17.0.

**Discussion::**

The trial will investigate whether the postoperative administration of YLS in patients with AMI after PCI will improve cardiac function. And it explores microRNAs (miRNA)-145 as detection of blood-based biomarkers for AMI by evaluating the relation between miRNAs in plasma and cardiac function.

**Trial registration::**

Chinese Clinical Trials Registry identifier ChiCTR2000038816. Registered on October 10, 2020.

Strengths and limitations of this studyThis is the first randomized, double-blinded, placebo-controlled, single-central clinical trial to explore the effectiveness and safety of Yiqi Liangxue Shengji prescription for the treatment of patients with acute myocardial infarction after percutaneous coronary intervention.Additive or synergistic cardioprotective effects of multiple, instead of single, cardioprotective agents will be better cardioprotective strategies to reduce myocardial infarction.This pilot study explores that in the setting of microRNAs -145 will be a novel biomarker for the diagnosis and prognosis of cardiovascular diseases and promising therapeutic strategy.This study is limited by the lack of clinical endpoints and the small sample size. Moreover, the trial will be undertaken in China, it is uncertain whether the similar effects are available to other ethnic groups and regions.

## Introduction

1

Despite recent progress in the diagnosis and treatment of cardiovascular diseases, coronary heart disease (CHD) represents the leading cause of death and disability worldwide.^[1,2]^ According to the WHO, CHD had caused 7,254,000 deaths worldwide (12.8% of all deaths) in 2008.^[3]^ After an acute myocardial infarction (AMI), timely and successful myocardial reperfusion with the use of thrombolytic therapy or percutaneous coronary intervention (PCI) is the most effective strategy for reducing the size of a myocardial infarct and improving the clinical outcome. However according to report, timely reperfusion by primary percutaneous coronary intervention (PPCI) and secondary preventative therapies still bring significant morbidity and mortality, with 7% death and 22% heart failure at 1 year.^[4]^ The process of restoring blood flow to the ischemic myocardium, however, can induce injury. The phenomenon of myocardial ischemia-reperfusion (MIR) injury can paradoxically reduce the beneficial effects of myocardial reperfusion.^[5]^ MIR often causes in further myocardial injury and cardiomyocyte death, which occurs in up to 50% of reperfused ST-segment elevation myocardial infarction patients, and its presence portends to a worse prognosis.^[6,7]^ And growing evidence from experimental studies MIR greatly contributes to the final infarct size.^[8,9]^ Although the process of myocardial reperfusion with advances in PCI technology that can timely and effective reperfuse coronary blood flow to ischemic myocardium or with antiplatelet and antithrombotic agents for maintaining the patency of the infarct-related coronary artery only reduce MIR,^[3]^ there currently remains no effective therapeutic agent for preventing MIR.^[4]^

Chinese herbal medicine (CHM), especially combined herbal formulations, has been widely used in traditional Chinese medicine for the treatment of myocardial infarction for hundreds of years and has attracted increasing attention in drug research.^[10]^ In the theory of Traditional Chinese Medicine (TCM), the collocation of monarch herbs and minister herbs is assembled according to the pathogenesis of patients with further prescription to adapt to the different pathogenesis of MIR. In the diagnosis of MIR, “blood stasis and heat syndrome” is an important syndrome based on the viewpoint of TCM theory and our previous clinical practice.^[11]^ TCM practitioners attach importance to preventing disease before it arises and controlling the development of existing disease. And, there are some special advantages for TCM in ameliorating myocardial ischemia-reperfusion injury.^[10]^

Yiqi Liangxue Shengji prescription (YLS) is a based on the TCM theory of “invigorating qi, activating blood and clearing up the heat of blood” for the prevention of MIR in China. Clinical trials have shown that YLS is effective in improving clinical symptoms and ameliorating the major adverse cardiovascular events (MACE) of coronary heart disease patients undergoing percutaneous coronary intervention.^[12,13]^ YLS consists of 4 herbal medicines (Table 1), including Astragalus membranaceus (Huang Qi), Salvia miltiorrhiza (Dan Shen), Cortex Moutan (Mudan Pi), Lonicerae japonicae flos (Jinyin Hua). Among them, Radix Astragali and Salviae Miltiorrhizae are the principal pharmacologically active components. They exhibit superior anticardiac reperfusion injury action in animals, including restoring cardiac mechanisms, such as coronary blood flow, lipid peroxide content, superoxide dismutase activity, the release of inflammatory mediators, and so forth, to favorable levels after reperfusion.^[14,15]^ However, there is no clinical evidence for YLS in the treatment of MIR. Therefore, we designed a randomized, double-blinded, placebo-controlled, single-central clinical trial aiming to evaluate cardiac protection from Yiqi Liangxue Shengji prescription in patients with AMI after PCI.

**Table 1 T1:** Components and dose of Yiqi Liangxue Shengji prescription.

Chinese name	English name	Pharmacological effects	Main active components	Weight (g/bag)	Reference
Huang Qi	Astragalus membranaceus	Anti-oxidation, regulation of mitophagy, anti-inflammation, immunomodulatory effects, anti-neurodegeneration,	Triterpene saponins (Astragalosides, Acetylastragaloside, AcetylastragalosideIsoastragaloside, Astramembrannin etc); Flavonoids (Isoflavonones, Isoflavans, Pterocarpans etc); Polysaccharides (Glucans, Heteropolysaccharide)	30	(Shan et al, 2019) (Liu et al, 2017)
Dan Shen	Salvia miltiorrhiza	Endothelial protective effects, proliferation and migration of VSMCs, improve microcirculatory, anticoagulant, antithrombotic, anti-inflammatory,	Diterpene chinone (tanshinone I–VI, cryptotanshinone, isotanshinone I–II, Danshenol A etc); phenolic acid (Danshensu, salvianolic acid A, salvianolic acid B, protocatechuic aldehyde, etc)	15	(Li et al, 2018)
Mudan Pi	Cortex Moutan	Anti-oxidative, anti-inflammatory, anti-tummor, vasodilatatory effects, improving blood circulation, inhibiting inflammation	paeonol, paeoniflorin, paeonoside, apiopaeonoside, oxypaeoniflorin, galloylpaeoniflorin, galloyloxypaeoniflorin, mudanpioside A, B, C, D, E, H, suffruticoside A, B, C, D, E, benzoyloxypaeoniflorin, benzoylpaeoniflorin and gallic acid, etc	10	(Wang et al, 2017)
Jinyin Hua	Lonicerae japonicae flos	Anti-inflammatory, bacteriostatic activity, antiviral activity, liver protective activity, anti-oxidative	Chlorogenic acids (Chlorogenic acid, Neochlorogenic acid, Isochlorogenic acid A, B, C, etc); Cinnamic acids (Caffeic acid, 3-O-Feruloylquinic acid etc); Benzoic acids (2,5-Dihydroxybenzoic acid-5-O-β-d-glucopyranoside)	10	(Li et al, 2019)

## Methods and design

2

### Patient and Public Involvement

2.1

Patients and/or public were not involved in the different stages of the study (including the design and the recruitment phase). However, we intend to disseminate the main results to trial participants and will seek patient and public involvement in the development of an appropriate method of dissemination.

### Study design

2.2

This is a single-central, randomized, double-blinded, placebo-controlled, parallel-group clinical trial. The study was registered at the Chinese Clinical Trial Registry on 10 October 2020 (ChiCTR2000038816). This study will be conducted in accordance with the principles of the Declaration of Helsinki and Good Clinical Practice guidelines. We will rigorously follow the latest Consolidated Standards of Reporting Trials (CONSORT 2017) for CHM recommendations,^[16]^ Standard Protocol Items: Recommendations for Interventional Trials and 2013 statement for herbal interventions.^[17]^ The study will recruit 140 AMI patients treated with PCI from inpatients and outpatients at the Dongfang Hospital, and has been approved by IRB of Dongfang Hospital Affiliated to Beijing University of Chinese Medicine (JDF-IRB-2020031102). All patients will provide written informed consent. The patient recruitment pathway is shown in Figure 1.

**Figure 1 F1:**
[figure not shown]
Study flowchart.

### Overall objective

2.3

The trial will investigate whether the postoperative administration of YLS in AMI patients treated with PCI will improve cardiac function. And it explores microRNAs (miRNA)-145 as detection of blood-based biomarkers for AMI by evaluating the relation between miRNAs in plasma and cardiac function.

### Patient inclusion and exclusion criteria

2.4

On arrival at the hospital, patients presenting AMI and treat with PCI will be screened for study eligibility and written informed consent will be obtained.^[18,19]^ Patients received standard secondary prevention treatment for coronary heart disease and Oral loading with 300 mg of Aspirin and clopidogrel hydrogen sulphate tablets (or 180 mg of ticagrelor) will be performed before surgery. Patient inclusion and exclusion criteria are listed in Table 2.

**Table 2 T2:** Patient inclusion and exclusion criteria for the trial.

Inclusion criteria
1. 18 yr old ≤ age ≤ 80 yr old.
2. Provision of written informed consent by participants or surrogates voluntarily.
3. Clinical diagnosis of acute myocardial infarction (AMI) occurred within 12 h,^[22]^ and all participants must have been treated with PCI.
4. Patients are diagnosed as having a syndrome of deficiency of Qi and blood stasis according to TCM standards.^[23]^
Exclusion criteria
1. Severe valvular heart disease (aortic stenosis), severe psychoneurosis, climacteric syndrome, hyperthyroidism, cervical spondylosis, gallbladder heart syndrome, gastro-oesophageal reflux disease.
2. Uncontrolled hypertension with systolic blood pressure ≥180 mm Hg or diastolic blood pressure ≥110 mm Hg, severe cardiac insufficiency with Ejection Fraction< 35%, severe arrhythmia (fast atrial fibrillation, atrial flutter, paroxysmal ventricular tachycardia, atrioventricular block higher than second degree subtype II, complete bundle branch block).
3. Patients with severe primary diseases like heart, brain, liver, kidney, hemopoietic system-related diseases, and patients whose Alanine Aminotransferase or Aspartate Transaminase is higher than 1.5 times of the upper limit, patients with renal insufficiency (serum creatinine > 194.5 μmol/L) or insulin-dependent diabetes mellitus.
4. Patients with depression or anxiety.
5. Stroke or resuscitated sudden death in the past 6 mo.
6. Patients with malignant tumor.
7. Pregnant women or breast feeding women.
8. Hyperthyroidism with TSH levels more than 1.5 times upper limit of normal.
9. Increased bleeding risk (gastrointestinal bleeding, traumatic head injury, and bleeding diathesis).
10. Patients with allergic constitution or are allergic to many kinds of TCM herbs and ingredients of the study drug.
11. Participation in other clinical trials in last 1 mo.
12. Patients unable or unwilling to sign the informed consent form.

PCI = percutaneous coronary intervention, TCM = Traditional Chinese Medicine.

### Removal, dropout, and termination criteria

2.5

Participants can voluntarily drop out at any time during the trial. Eligible subjects failing to complete the observation period presented in the trial will be considered as dropout cases regardless of the time and reason. Reasons for dropout will be recorded, and the last data recorded for these participants will be included in the data analysis. The trial will be suspended in a specific participant if serious adverse events (AEs) relevant to the YLS occur; the participant decides to join in another clinical research project in terms of cardiovascular diseases; the participant demonstrates hypersensitivity toward YLS, such as abnormal thirsty, stomach ache, and diarrhoea; the participant suffers from acute life-threatening disease. The whole research would be terminated in the following circumstances: masking of the randomization fails; unblinding rate exceeds 20% of the sample size; assessments of all follow-up are completed.

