#### Safety outcomes

2.8.2

Safety is assessed by vital signs, laboratory examinations, and AEs. Vital signs include body temperature, breathing, blood pressure, and heart rate. Laboratory examinations include blood, urine and stool routine, liver, and kidney function. AEs will be recorded all the time during the treatment. The development of AEs will also be observed until the adverse reactions disappear.

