### Statistical analyses

2.11

The statistical analyses of primary and secondary outcomes will be conducted in both the intention-to-treat set and the per-protocol set. Primary and secondary endpoint data will be collected for the entire follow-up period for all patients. Patients lost to follow-up will be considered at risk until the date of last contact, at which point they will be censored. In the per-protocol set, patients who undergo randomization but withdraw consent to participate or not treated according to the allocated procedure after randomization will be excluded from per-protocol statistical analyses.

IBM SPSS V17.0 software pack was used for data analysis. The normal distribution of the data was tested with Pearson test. Independent sample *t* test was used for the comparison of data with normal distribution, while Spearman test was used for the comparison of data without normal distribution. Data with normal distribution were expressed as arithmetic mean ± standard deviation, while data without normal distribution were expressed as median value (minimum–maximum). A *P* value between .1 and .05 was considered marginally significant, a *P* value between .01 and .05 was considered significant, .001 and .01 highly significant, and < .001 very highly significant.

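### Section 2.5 takes participants with reactions attributed to YLS out of the trial and analyses their last recorded data, which is inconsistent with section 2.11's collection of endpoint data in all patients

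*Protocol article*

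**What the plan says.** Section 2.5 (Removal, dropout, and termination criteria) fixes three things.

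- Who counts as a dropout: "Eligible subjects failing to complete the observation period presented in the trial will be considered as dropout cases regardless of the time and reason".
- What happens to their data: "Reasons for dropout will be recorded, and the last data recorded for these participants will be included in the data analysis".
- When an individual's participation is halted. The list opens with "The trial will be suspended in a specific participant if serious adverse events (AEs) relevant to the YLS occur". It continues with "the participant decides to join in another clinical research project in terms of cardiovascular diseases" and "the participant demonstrates hypersensitivity toward YLS, such as abnormal thirsty, stomach ache, and diarrhoea", and ends with acute life-threatening disease.

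Section 2.11 (Statistical analyses) takes a different line: "Primary and secondary endpoint data will be collected for the entire follow-up period for all patients". Analyses are run in the intention-to-treat and per-protocol sets. Those who withdraw consent or are "not treated according to the allocated procedure after randomization will be excluded from per-protocol statistical analyses", so departure from allocated treatment is a reason for exclusion from the per-protocol set only.

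On safety, section 2.8.2 adds: "The development of AEs will also be observed until the adverse reactions disappear". It does not mention the efficacy endpoints. Section 2.8.3 schedules NT-proBNP and LVEF at baseline and 8 weeks. Table 3 shows a treatment-period column covering weeks 4 to 8, and section 2.10 mentions an echocardiogram at 1 month.

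**The concern.** Take a participant who stops the granules in week 2 because of diarrhoea attributed to YLS. Under section 2.5 that person appears to leave the trial, and the last recorded value stands in for the outcome. Under section 2.11 the same person is followed and has a week-8 measurement. A site cannot do both.

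If section 2.5 is followed, an obtainable week-8 NT-proBNP or LVEF may be replaced by an earlier value, often baseline, which is an imputed change of zero. The trigger is a tolerance-related event after randomisation, so its frequency may differ between arms. The rule governs conduct as well as analysis: a visit that was never held cannot be recovered by a later analysis plan.

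**Working it through.** **1. The two rules side by side**

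| Question | Section 2.5 | Section 2.11 |
|---|---|---|
| Does a participant with a YLS-attributed reaction continue? | The trial is suspended for that person; continued assessment is not mentioned | Endpoint data are collected in all patients throughout |
| Which value enters the analysis? | The last recorded data | The collected endpoint; loss to follow-up is censored at last contact |
| Consequence of not being treated as allocated | Not separated from leaving the trial | Exclusion from the per-protocol set only |

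The censoring sentence does not settle the matter. Censoring suits time-to-event data such as MACE; it does not say which week-8 NT-proBNP or LVEF value to use.

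Two features favour reading suspension as leaving the trial: the section heading speaks of removal, and the list includes joining another cardiovascular study, which is a reason to leave a trial and not a reason to stop a drug.

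**2. The plan's own figures**

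Inputs from section 2.7: P1 = 0.32, P2 = 0.58, mean P = 0.45, printed constants 1.65 and 1.28.

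n = (1.65 + 1.28)² × 2 × 0.45 × 0.55 / 0.26² = 8.585 × 0.495 / 0.0676 = 62.9, so 63 per arm and 126 in total. This reproduces the plan. Recruitment is 140, that is 70 per arm, and the 10% dropout allowance is 14 participants.

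**3. Illustration of size for NT-proBNP**

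Assumptions, none given in the document: 32% and 58% are treated as mean percentage reductions; *a* YLS and *b* placebo participants are removed; stoppers in both arms would have shown the same reduction *r* at week 8; baseline is carried forward for all of them.

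- Difference with observed values: [0.58(70 − a) + r·a]/70 − [0.32(70 − b) + r·b]/70
- Difference with baseline carried forward: 0.58(70 − a)/70 − 0.32(70 − b)/70
- Bias (second minus first): −r(a − b)/70

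Worked case, 9 and 5 removed, r = 0.32. Observed: (35.38 + 2.88)/70 − (20.80 + 1.60)/70 = 22.66 points. Carried forward: 35.38/70 − 20.80/70 = 20.83 points. Bias: −1.83 points.

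Bias in percentage points (negative = against YLS):

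| Removed, YLS / placebo | Stoppers would have fallen 32% | Unchanged | Risen 32% |
|---|---|---|---|
| 7 / 7 | 0 | 0 | 0 |
| 9 / 5 | −1.8 | 0 | +1.8 |
| 10 / 4 | −2.7 | 0 | +2.7 |
| 5 / 9 | +1.8 | 0 | −1.8 |
| 3 / 1 | −0.9 | 0 | +0.9 |

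If only half of those removed fall back to baseline and the others hold a value equal to week 8, the entries halve: 0.9 for 9/5 and 5/9, 1.4 for 10/4. For any split of 14 with stopper changes within ±32%, the limit is 0.32 × 14/70 = 6.4 points.

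Equal removal alone does not guarantee zero. If stoppers at 7/7 would have reached their own arm's planned mean, the bias is −(0.58 × 7 − 0.32 × 7)/70 = −2.6 points, so 26 becomes 23.4.

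**The case against.** The case against has real substance.

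- **The wording is not decisive.** Section 2.5 says suspended for a participant and terminated for the whole study, and never states that assessments stop. Including the last recorded data could mean only that data gathered up to departure are kept. Someone who stops the granules but attends week 8 is not clearly a dropout. This stands as a limit on certainty: leaving the trial and carry-forward are the likelier readings, not explicit ones.
- **The intention-to-treat analysis is not breached.** A reader might infer that section 2.5 contradicts it. It does not: using last recorded data keeps the participant in the set. The inconsistency is with collecting endpoint data in everyone for the whole follow-up.
- **Missing-data methods belong in the analysis plan.** True in general, but here the article states a rule, and part of that rule decides whether a visit takes place.
- **The size is assumed.** This stands. The 14 cover every dropout reason, so these triggers would account for only part of them; 3/1 may be nearer the mark. Some participants will have a later value from Table 3's window or, for LVEF, the 1-month echocardiogram.
- **The model differs from the plan's formula**, which treats 32% and 58% as proportions. On that reading, with *q* the share of stoppers who would have responded and baseline counted as non-response, the bias is −q(a − b)/70. It can then only run against the arm with more removals, and the right-hand column of the table does not apply.

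**Conclusion.** The point holds as an unreconciled inconsistency between sections 2.5 and 2.11 on whether participants stopped for tolerance reasons are still measured. It is worth correcting, with moderate confidence, because it rests on the natural but not explicit reading of section 2.5.

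A reader might infer that the rule is bound to favour YLS, or bound to disadvantage it. The document supports neither: it gives no removal rates and no information on how stoppers fare. If more YLS than placebo participants are removed, the bias runs against YLS when they would have improved and towards YLS when they would have worsened, as is possible after a serious adverse event. It is nil when removals are equal and stoppers in both arms respond alike. The table's figures show what is possible under stated assumptions and are not estimates for this trial. No change in sample size follows.

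**What to change.** In section 2.5, separate stopping study medication from leaving the study:

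- State that serious adverse events, hypersensitivity reactions and acute intercurrent disease, in either arm, stop study medication only. Writing study medication in place of YLS is a wording correction, since blinding is already covered in section 2.6.
- State that week-8 NT-proBNP and LVEF, and MACE, are still collected unless the participant withdraws consent.
- State that the intention-to-treat analysis uses the observed week-8 values in place of the last recorded value.
- Treat joining another cardiovascular trial separately: follow these participants where they agree and record the event, because their later values may reflect another intervention.

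This takes a few sentences and brings section 2.5 into line with section 2.11. The week-8 assessment is already scheduled, so the cost is a few more retained visits. It has to be settled before visits are missed.

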#### Primary and secondary outcomes

2.8.3

The primary outcome measures of the study are NT-proBNP and left ventricular ejection fraction, which will be measured at baseline and 8 weeks after randomization. Secondary outcomes include plasma levels of microRNA-145, plasma creatine kinase-MB, and CardiaC Troponin I levels in blood samples. At the same time, the trial also observes the occurrence of MACEs defined as the composites of deaths from any cardiac causes, myocardial infarction, and revascularization (PCI or CABG) at 8 weeks after randomization. The efficacy of angina symptoms, Seattle Angina Questionnaire, will be recorded at baseline and 8 weeks after randomization and TCM syndrome efficacy.^[24]^ Items to be measured and the time window of data collection are shown in Table 3.

**Table 3 T3:** Schedule of data collection.

Items	Screening period within 1 wk	Treatment period 4–8 wk	Follow-up period 2–12 mo
Signed informed consent	√		
Inclusion/exclusion criteria	√		
Demographic data	√		
Medical history, course of disease, treatment history	√		
Combined diseases	√		
Concomitant medications	√	√	
LVEF	√	√	
NT-proBNP	√	√	
microRNA-145	√		
CK-MB	√		
cTnI	√		
MACEs			√
SAQ	√	√	
TCM syndrome efficacy	√	√	
Vital signs	√	√	
Blood, urine and stool routine	√	√	
Liver and kidney function	√	√	
Adverse events		√	√

Vital signs: temperature, heart rates, breathing, and blood pressure.

CK-MB = creatine kinase-MB, cTnI = CardiaC Troponin I, LVEF = left ventricular ejection fraction, MACE = major adverse cardiac event, SAQ = Seattle Angina Questionnaire, TCM = Traditional Chinese Medicine.

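### For patients who leave before week 8, the last-value rule puts the acute baseline into the NT-proBNP analysis, and the censoring rule in section 2.11 cannot serve either primary outcome

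*Protocol article*

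**What the plan says.** Section 2.5 defines dropout broadly: "Eligible subjects failing to complete the observation period presented in the trial will be considered as dropout cases regardless of the time and reason". For these patients, "the last data recorded for these participants will be included in the data analysis".

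Section 2.8.3 names the primary outcomes and their timing: "NT-proBNP and left ventricular ejection fraction, which will be measured at baseline and 8 weeks after randomization". The baseline belongs to the acute phase. Table 2 requires "Clinical diagnosis of acute myocardial infarction (AMI) occurred within 12 h", and Table 3 places the first measurements in a screening period of one week.

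Section 2.11 plans intention-to-treat and per-protocol analyses and states: "Primary and secondary endpoint data will be collected for the entire follow-up period for all patients". The next sentence gives a second rule: "Patients lost to follow-up will be considered at risk until the date of last contact, at which point they will be censored". Continuous data are to be compared by t test if normally distributed. No time-to-event method is named.

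Two other places bear on the point. Section 2.10 mentions echocardiograms at 1 and 12 months, and Table 3 heads the treatment column 4–8 weeks.

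**The concern.** With a baseline and one endpoint measurement, carrying the last value forward amounts to carrying the baseline forward for anyone who leaves before the endpoint. For NT-proBNP after an infarct, that value contradicts the plan's own expectation, because section 2.7 assumes a 32% reduction on routine treatment. It does not matter whether changes or week-8 levels are compared, since the early leaver's week-8 level is set equal to the acute level in both cases.

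Dropout may also be related to treatment or outcome. Section 2.5 ends participation for YLS-related serious adverse events, for hypersensitivity and for acute life-threatening disease. If early loss differs by arm, the filled-in values shift the comparison even when the treatment does nothing.

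The censoring sentence gives no alternative. It is not limited to events and follows directly on a sentence about primary and secondary endpoints, but a continuous value at week 8 cannot be censored at last contact. As written, the analyst has one rule that biases the primary comparison and another that cannot be applied to it.

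**Working it through.** **Inputs.** All are from section 2.7 unless marked.
- Expected NT-proBNP reduction: 32% on routine care, 58% with YLS, so a difference of 26 points.
- Dropout: 10% overall, with no timing and no split by arm.
- Planned size: 63 per arm (126), 138 after dropout, 140 recruited.
- Assumptions made here: all dropout occurs before week 8 (an upper case); early leavers would have had their arm's average reduction; the splits 15/5 and 5/15 are illustrations.

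**Plan's own figure.** With P = (0.32 + 0.58)/2 = 0.45:

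n = (1.65 + 1.28)² × 2 × 0.45 × 0.55 / 0.26² = 8.5849 × 0.495 / 0.0676 = 62.86, so 63 per arm.

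Then 126 × 1.1 = 138.6 and 126/0.9 = 140, in line with 138 and 140. The figure reproduces with the printed 1.28, which is the value for β = 0.1 rather than the stated 0.2. That is a separate matter. At 10%, about 14 of 140 patients drop out.

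**Effect of carrying baseline forward.** A share d of an arm enters with zero reduction, so the expected mean reduction is (1 − d) × m, where m is the arm's true mean reduction.

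| Dropout YLS / placebo | YLS | Placebo | Difference |
|---|---|---|---|
| 0 / 0 | 58.0 | 32.0 | 26.0 |
| 10% / 10% | 0.90 × 58 = 52.2 | 0.90 × 32 = 28.8 | 23.4 |
| 15% / 5% | 0.85 × 58 = 49.3 | 0.95 × 32 = 30.4 | 18.9 |
| 5% / 15% | 0.95 × 58 = 55.1 | 0.85 × 32 = 27.2 | 27.9 |

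**No true effect (32% in both arms).** At 15% YLS / 5% placebo: 27.2 − 30.4 = −3.2 points, against YLS. At 5% / 15%: 30.4 − 27.2 = +3.2 points, in favour of YLS.

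**Rough consequence for the test.** This treats the percentages as proportions, as section 2.7 does, with 70 per arm and one-sided 0.05. Rejection probability = Φ[(D − 1.645 × SE₀)/SE₁], where D is the expected difference as a proportion and SE₀ and SE₁ are the pooled and unpooled standard errors.
- No dropout: 93%.
- 10% / 10%: (0.234 − 1.645 × 0.0830)/0.0806 = 1.21, so 89%.
- 15% YLS / 5% placebo: 74%.
- No true effect, 5% YLS / 15% placebo: (0.032 − 1.645 × 0.0765)/0.0765 = −1.23, so 11% instead of 5%.

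These probabilities are a guide only, because NT-proBNP is continuous and the documents give no standard deviation.

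**LVEF.** The documents give no expected change, so no size can be calculated. A 1-month value carried to week 8 would still precede the endpoint.

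**The case against.** A fair defence has several parts.

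- **Carry-forward is not named.** Section 2.5 could mean only that data collected before dropout are kept. That is possible, but including the last recorded data in the analysis is most naturally read as using it for the missing endpoint. The wording needs settling either way.
- **Many dropouts may be unaffected.** A reader might infer that every dropout enters with the baseline. The text does not support that. Dropout is defined over the whole observation period, which runs 12 months past treatment, and anyone who leaves after week 8 already has the endpoint. Section 2.8.3 does not say that there are no other measurements. Section 2.10 gives a 1-month echocardiogram, and the 4–8 week column of Table 3 leaves room for an intermediate value of either outcome. This limits the point to early leavers, and makes it firmer for NT-proBNP than for LVEF.
- **The two rules may not collide.** At risk and censored are terms for events, and MACE is a secondary outcome. On that reading, section 2.5 covers measurements and section 2.11 covers events. This stands in part: what is missing is a statement of scope. It does not rescue carry-forward.
- **Collection is already promised for all patients.** This stands. Section 2.11 says so, and suspending a participant under section 2.5 need not end outcome measurement. The week-8 visit after stopping is a clarification rather than a new commitment.
- **The bias need not favour YLS.** A reader might infer a risk of a false positive from the withdrawals for YLS reactions. Extra loss in the YLS arm works against YLS. A spurious benefit needs more early loss on placebo, for which the documents give no particular reason.
- **Standard error.** A reader might infer that filling in values makes the standard error too small. The documents do not show this, because zeros also add spread. With 10% dropout in each arm and a common SD s, the carry-forward error is below the complete-case error only if 0.81 × (2s² + 0.1 × (58² + 32²)) < 2s², that is, s above about 31 points. No SD is given.

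The matter is not one left to a separate analysis plan, because the article itself states both rules.

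**Conclusion.** The concern holds for patients who leave before week 8. On the natural reading of section 2.5, their acute baseline would stand in for the week-8 NT-proBNP value, against the plan's own expected 32% fall; for LVEF, an early echocardiogram may stand in instead. Censoring as written in section 2.11 cannot apply to either primary outcome.

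At the only documented rate, equal by arm and all before week 8, the cost is 2.6 of 26 points (26.0 − 23.4), which is modest. The larger worry is unequal early loss: the expected difference then ranges from 18.9 to 27.9 points under the assumed splits, and a 3.2-point difference arises with no true effect, against whichever arm loses more. Carry-forward therefore cannot be relied on to be conservative. The sizes rest on the assumed timing and splits, and on early leavers resembling their arm's average.

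**What to change.** Make four changes to the wording before unblinding.

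1. In section 2.5, delete the last-value rule for NT-proBNP and LVEF.
2. In section 2.11, state that the commitment to collect endpoint data for all patients includes the week-8 NT-proBNP and LVEF of those who stopped study drug.
3. Analyse the week-8 values adjusted for baseline (ANCOVA), with multiple imputation by arm under missing at random, or an equivalent likelihood method. Add a delta-adjusted sensitivity analysis that shifts the imputed values, also by different amounts in the two arms.
4. Limit the censoring sentence to MACE.

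The cost is protocol wording, a little more analysis work, and the effort of following patients who stopped treatment to week 8. At the planned rate this concerns at most about 14 of 140 patients.
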